**3.6.3 PHASE THREE: THE IMPLEMENTATION OF THE INTERVENTION**

**3.6.3.1. Aim:** To conduct the feeding trial using the *Curcubita Moschata* snack meal and the song.

**3.6.3.2. Objectives**:

3.6.3.2.1. To feed the children with the intervention or control for six months

- - - - 1. To assess adherence to the dietary intervention in terms of consuming Cucurbita *moschata* seed paste

**3.6.3.3. Design:** Study design will be a pretest-posttest control group trial, using cluster randomisation, which is a type of scientific experiment, which aims to reduce bias when testing a new treatment (Leedy and Ormrod, 2010). The preschools participating in the trial are randomly allocated either to the group receiving the treatment under investigation or to a group receiving standard treatment (or placebo treatment) as the control (Leedy and Ormrod, 2010). Randomized minimizes selection bias and the different comparison groups allow the researchers to determine any effects of the treatment when compared with the no treatment (control) group, while other variables are kept constant (Leedy and Ormrod, 2010). Randomization will take place at the preschool level. The research will be using single blinded trial with a knowledge of who is receiving the treatment amongst the participants.

- - - 1. **Intervention and data collection:**

The experimental group will receive their normal diet plus paste (grounded *Cucurbita moschata* seeds mixed with cooked *Cucurbita moschata* flesh) and the educational lesson through the song for six (6) months while the control group will receive normal diet plus mashed *Cucurbita moschata* flesh. The participants will consume ½ cup (64 g) (***to be confirmed after development and pilot***) paste (grinded *Cucurbita moschata* seeds mixed with mash *Cucurbita moschata* flesh) twice per week, during lunch with their normal diet while the control will consume mashed *Cucurbita moschata* flesh at the preschool sites over a six (6) month period. Two dishes made from grinded *Cucurbita moschata* seeds mixed with *Cucurbita moschata flesh* will be used to bring variety and improve compliance.

Grounded *Cucurbita moschata seeds* will be packaged at the food science laboratory at the university of Venda before being delivered to preschools. The packaged grounded *Cucurbita moschata seeds will be mixed with cooked Cucurbita moschata flesh at the preschool site. Mashed Cucurbita moschata flesh mixed with grinded seeds and Mashed Cucurbita moschata flesh* will be served to children during their lunchtime under the supervision of the researcher and trained field worker.

Promotion of the consumption of the seeds and nutrition education will be done in the form of a song, which is known to be the best method for educating children under the age of five years. The training on the consumption of the seeds will involve the guardian/parents during participant’s recruitment because children at this age are still fully dependent for food on their caregivers/parents who thus influence their eating habits (Curtis *et al*., 2011). The focus of the training will be on the health benefits of consuming seeds of *Cucurbita* *spp.* The songs will be easily learned by preschool children and will become favourites because of their familiarity. Furthermore, the songs will build confidence in preschool children and even shy children are likely to participate as part of a group or whole class. The recorded lyrics during the Pilot will be used. The table below is a schematic representation of the feeding trial.

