**2.2. Hypothesis**

A null and an alternate hypothesis have been determined.

**Null hypothesis:** Consumption of *Cucurbita moschata* seed paste does not improves zinc and iron status in deficient children.

**Alternative hypothesis:** Consumption of *Cucurbita moschata* seed paste improves zinc and iron status in deficient children.

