**2.3. Main aim of the study**

The primary aim of this study is to test the efficacy of consumption of *Cucurbita moschata* (Butternut) seeds in improving zinc and iron status in preschool children in the Vhembe district, Limpopo province of South Africa, and the secondary aim is to describe the nutritional, zinc and iron status of the children. To attain the aims of this study the following objectives have been developed. Objectives of this study are outlined in each phase

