**2.5. Expected outcomes**

- Zinc and iron status of the intervention group will improve from baseline levels after consumption of the seeds for 6 months.
- Eating patterns of the participants will improve because of the nutrition education.
- Consumption of fruits and vegetables will increase because of the nutrition education.

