**Table 3.3: Schematic representation of the feeding trial.**

| **Group** |  | **Estimated no** | **Intervention** | **Intervention days (three teams)** | **Quality control** |
| --- | --- | --- | --- | --- | --- |
| Experimental | Preschool 1 | 73 | Normal diet plus seed paste.  Song | Monday  Wednesday | Plate wastage observations and adherence recording |
|  | Preschool 2 | 73 | Normal diet plus seed paste  Song | Tuesday  Thursday | Plate wastage observations and adherence recording |
|  | Preschool 3 | 73 | Normal diet plus seed paste  Song | Monday  Thursday | Plate wastage observations and adherence recording |
|  | Preschool 4 | 73 | Normal diet plus seed paste  Song | Wednesday  Friday | Plate wastage observations and adherence recording |
| Control | Preschool 5 | 73 | Normal diet plus mashed butternut (placebo) | Monday  Wednesday | Plate wastage observations and adherence recording |
|  | Preschool 6 | 73 | Normal diet plus mashed butternut (placebo) | Tuesday  Thursday | Plate wastage observations and adherence recording |
|  | Preschool 7 | 73 | Normal diet plus mashed butternut (placebo) | Monday  Thursday | Plate wastage observations and adherence recording |
|  | Preschool 8 | 73 | Normal diet plus mashed butternut (placebo) | Wednesday  Friday | Plate wastage observations and adherence recording |

The intervention will be implemented over six months or 180 days. On intervention days, Monday to Thursday, the field workers and the researcher will be on site for quality control. They will work in teams of two, one team per preschool. The researcher will change team daily to ensure standardisation and quality control**.**

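### The nutrition song is given only in the experimental preschools, so the trial tests seed paste plus education, while its aim and hypothesis credit the seeds alone; the parent training is also not tied to an arm

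*Protocol*

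**What the plan says.** **The claim.** Section 2.3 states: "The primary aim of this study is to test the efficacy of consumption of" the seeds in improving zinc and iron status. The alternative hypothesis in 2.2 is that consuming "seed paste improves zinc and iron status in deficient children". Neither names education.

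**The arms.** Section 3.6.3 gives the experimental group normal diet plus paste "and the educational lesson through the song for six (6) months while the control group will receive normal diet plus mashed" butternut flesh. The schematic table of the feeding trial agrees: the song stands in every experimental row and in no control row. The design paragraph of the same section says that comparison groups show the effect of treatment "while other variables are kept constant".

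**The intervention as defined elsewhere.** The phase-one aim (3.6.1.1) is to develop an intervention made up of a snack and nutrition education. The phase-three aim (3.6.3.1) is a feeding trial using the snack meal and the song.

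**What the education is expected to do.** Section 2.5 expects better eating patterns, and states: "Consumption of fruits and vegetables will increase because of the nutrition education".

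**Parent training.** Section 3.6.3 says: "The training on the consumption of the seeds will involve the guardian/parents during participant’s recruitment", with the health benefits of the seeds as its focus. Recruitment (3.6.2.4) covers all the selected preschools.

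**The concern.** Both arms eat butternut flesh and only the experimental arm gets ground seed, so the control dish looks built to isolate the seeds. Giving the song to one arm undoes that. If zinc or iron status improves more in the experimental preschools, the stated conclusion, that the seeds did it, does not follow from the design.

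The parent training adds a second uncertainty. It promotes a food that the protocol says is now mostly discarded, at a stage common to all preschools, and no section says which parents receive it. A difference between arms, or the lack of one, could then partly reflect seed use or other dietary change at home.

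**Working it through.** The point concerns design, and no figure in the protocol changes because of it. The check sets the sections side by side.

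1. **What differs between arms.** Experimental: normal diet, flesh, seeds, song. Control: normal diet, flesh. Two components differ: seeds and song. The statement that other variables are held constant is therefore not met.

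2. **Whether the two can be separated.** In the schematic table the song is present in 4 of 4 experimental preschools and 0 of 4 control preschools. Section 3.4 plans six preschools, with two more if numbers fall short, but the rule is the same for six or eight. Song and seeds coincide exactly at the unit of randomisation. No regression or ANOVA (3.6.4.4) can separate them, so this cannot be left to a statistical analysis plan.

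3. **Whether the song offers another route to the outcome.** The protocol supplies the links. Section 2.5 expects education to raise fruit and vegetable intake. Section 1.6.1 names vegetables and fruits as sources of iron and zinc, and says that foods with vitamin C increase absorption of non-heme iron.

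4. **Illustration of scale, under assumptions not in the protocol.** The planned sample reproduces: 40291 / (1 + 40291 × 0.05²) = 40291 / 101.7275 = 396.07, so 396. Assume an equal split (198 per arm), an outcome in SD units, two-sided 5% testing and no clustering. The standard error of the difference is √(2/198) = 0.1005. With a seed effect of zero and an education effect e, the chance of a significant difference is Φ(e/0.1005 − 1.96) + Φ(−e/0.1005 − 1.96):
   - e = 0: 5%
   - e = 0.05 SD: 8%
   - e = 0.10 SD: 17%
   - e = 0.20 SD: 51%

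   These values of e are assumed. Allocation is by preschool, so the percentages show the mechanism only and are not forecasts.

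5. **Parent training, both readings.** Section 3.6.2.4 recruits in all selected preschools, with a parents' meeting at visit 2 and data collection at visits 3 and 4. Section 3.4 does not say whether allocation comes before or after recruitment.
   - If all parents are trained, control children may eat seeds at home and the contrast shrinks.
   - If only experimental parents are trained, a third component coincides with the arm.

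   Either way the seed contrast is compromised, and the protocol does not say which case applies.

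**The case against.** The strongest reply is that the package is declared: 3.6.1.1 and 3.6.3.1 both define the intervention as snack plus education, and randomised arms estimate the effect of that package without confounding. This stands, and it makes a restated claim a sufficient remedy. It does not rescue the aim and hypothesis as written.

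The dietary route through the song may also be weak. The English lyrics in 3.6.1.6 mention only butternut, its seeds, zinc and iron, and section 3.6.3 says that children of this age depend on caregivers for food. This limits the likely size of the effect. It does not remove a pathway that 2.5 itself predicts.

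Three stronger readings are tempting, and the protocol does not support them:

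- *The control arm is contaminated.* A reader might infer this from training during recruitment. No section says that control parents are trained, and the visit 2 description mentions explanation and consent only. Home seed use would also be visible: the FFQ covers the seeds (3.6.2.5, Appendix D) and is repeated after the trial (3.6.4.2), and home food diaries run for six months (3.6.3.5). "Open to contamination" is as far as the text goes.
- *The sample must grow by a known factor.* If a share c of control children took up seeds at a similar dose, the multiplier would be 1/(1 − c)²: 1.23 at c = 0.10 and 2.04 at c = 0.30. These shares are pure assumption, the sample rests on no stated power or effect size, and the formula ignores allocation by preschool.
- *Participants are unblinded by design.* The sentence "The research will be using single blinded trial with a knowledge of who is receiving the treatment amongst the participants" is ambiguous. It can mean that the researcher knows who among the participants is treated. It needs clearer wording but is secondary here.

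**Conclusion.** The concern holds in this form: the randomised comparison estimates the effect of seed paste plus education, while the hypothesis and primary aim claim an effect of seeds alone. This rests on the text of 2.2, 2.3, 2.5 and 3.6.3 and needs no assumption. The overlap of the two components is total by allocation. The share of any difference that is due to education is unknown and cannot be derived from the protocol.

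The parent-training point is conditional. As written, the contrast is open to dilution if control parents are trained, or to further confounding if only experimental parents are. Neither is shown to occur, and no sample-size consequence should be attached to it.

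The song imbalance should be settled before the intervention starts, and the training before parents are recruited. After data collection the claim can be narrowed, but the components cannot be separated.

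**What to change.** 1. **Choose one claim.** Either (a) play a song in the control preschools with the seed content removed, and keep the seed aim; or (b) keep the song in one arm and restate the aim, hypothesis and conclusion as seed paste plus nutrition education. Option (a) costs one edited recording; recordings for each preschool are already planned in 3.6.1.6. Option (b) costs only wording, but the claim is narrower. Under (b), also correct the statement about other variables being constant.

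2. **Tie the parent training to time and arm.** State the order of allocation and recruitment. Under (b), train parents in the experimental preschools only, after baseline bloods and allocation, and offer the session to control parents after the endline survey. Under (a), defer it in both arms until after the endline survey. This moves one parents' session. Control parents will still learn of the seeds through the full explanation required for consent (3.9), so the change reduces promotion to them without removing awareness.

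3. **Use the data already planned.** Compare home seed intake by arm from the FFQ and the food diaries; section 3.6.3.6 now plans only frequencies for the diaries. No new data collection is needed.

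4. **Secondary wording.** Rewrite the blinding sentence to say who is blinded and who is not.

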**Table 3.3: Schematic representation of the feeding trial.**

| **Group** |  | **Estimated no** | **Intervention** | **Intervention days (three teams)** | **Quality control** |
| --- | --- | --- | --- | --- | --- |
| Experimental | Preschool 1 | 73 | Normal diet plus seed paste.  Song | Monday  Wednesday | Plate wastage observations and adherence recording |
|  | Preschool 2 | 73 | Normal diet plus seed paste  Song | Tuesday  Thursday | Plate wastage observations and adherence recording |
|  | Preschool 3 | 73 | Normal diet plus seed paste  Song | Monday  Thursday | Plate wastage observations and adherence recording |
|  | Preschool 4 | 73 | Normal diet plus seed paste  Song | Wednesday  Friday | Plate wastage observations and adherence recording |
| Control | Preschool 5 | 73 | Normal diet plus mashed butternut (placebo) | Monday  Wednesday | Plate wastage observations and adherence recording |
|  | Preschool 6 | 73 | Normal diet plus mashed butternut (placebo) | Tuesday  Thursday | Plate wastage observations and adherence recording |
|  | Preschool 7 | 73 | Normal diet plus mashed butternut (placebo) | Monday  Thursday | Plate wastage observations and adherence recording |
|  | Preschool 8 | 73 | Normal diet plus mashed butternut (placebo) | Wednesday  Friday | Plate wastage observations and adherence recording |

The intervention will be implemented over six months or 180 days. On intervention days, Monday to Thursday, the field workers and the researcher will be on site for quality control. They will work in teams of two, one team per preschool. The researcher will change team daily to ensure standardisation and quality control**.**

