***(a) Grounded Cucurbita moschata seeds mixed cooked flesh and sugar***

After the seeds are removed from *Cucurbita moschata,* they will be rinsed with water to remove any strings and bits of squash. The seeds will be patted dry and placed in a small bowl. Once the seeds are dried they will be grounded in a machine until they form a powder*. The skin of Cucurbita moschata* will be peeled off and the flesh will be chopped into cubes, chopped flesh of *Cucurbita moschata* will be cooked with 2 cups of water and 30g of sugar. The cooked *Cucurbita moschata* will be mixed with the powder (grounded seeds) to make a paste.

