**(b)** ***Paste mixed with cinnamon***

The cooked *Cucurbita moschata* will be mixed with the powder (grounded seeds) to make a paste. Cinnamon will be added to paste to enhance flavour and taste.

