**(c) *Paste mixed with vanilla essence and honey.***

Vanilla essence and honey in the food increase the appearance, flavour and taste. The same procedures as in (a) will be followed, except that the sugar will be replaced with honey.

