**(d) *Paste cooked with butter***

Butter also known to add flavour and taste to food. Fats assist in the absorption of vitamins. Same procedure as in (a) above.

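### The seed dishes are flavoured, chosen for liking and served in two varieties, but the control called a placebo is one mashed-flesh food with no recipe or portion, which weakens attribution to the seeds

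*Protocol*

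**What the plan says.** **Experimental food.** Section 3.6.1.5 describes four candidate seed dishes.

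- (a): the flesh "will be cooked with 2 cups of water and 30g of sugar" before the seed powder is mixed in.
- (b): "Cinnamon will be added to paste to enhance flavour and taste".
- (c): vanilla essence and honey; the procedure of (a) "will be followed, except that the sugar will be replaced with honey".
- (d): "Butter also known to add flavour and taste to food", otherwise prepared as (a).

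Children say which dishes they like best, and the two favourites become the trial food (3.6.1.5(e) and 3.6.1.8). Section 3.6.3 explains that two dishes are used for variety and better compliance. It gives a portion of ½ cup (64 g) for the paste, still to be confirmed after development and pilot.

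**Control food.** Section 3.6.3 says that "the control group will receive normal diet plus mashed" butternut flesh. The schematic table (headed Table 3.3) lists it as "Normal diet plus mashed butternut (placebo" for each control preschool. No cooking procedure, added ingredient, second dish or portion is given.

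**Other differences.** The song is part of the experimental arm only (section 3.6.3 and the schematic table). Monthly sensory evaluation takes place in the experimental preschools only (3.6.3.5).

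**Claim to be supported.** The main aim (2.3) and the phase four aim (3.6.4.1) concern the efficacy of the seeds. The hypothesis (2.2) is worded in terms of the seed paste.

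**The concern.** To credit a between-arm difference to the seeds, the control food should be the experimental food with the seeds left out. As written, one food has been flavoured and selected because children like it, and it alternates between two dishes. The other is a single food that nobody has taste-tested and whose preparation is not described. No later analysis can separate seeds from recipe, because every experimental preschool receives both together.

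Two kinds of result are most plausibly affected:

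- **Anthropometry.** Weight, height and MUAC are measured again in phase four, and section 3.6.4.4 compares experimental with control. Sugar, honey or butter given in one arm only is an alternative explanation for a difference.
- **Intake.** The schematic table records plate waste in both arms. If one food was optimised for liking and the other was not, a difference in waste says nothing clear about how acceptable the seeds are.

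The placebo label also promises a closer match than the text delivers.

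**Working it through.** No figure in the protocol bears directly on this point, and the sample size does not enter it. The check sets the two foods side by side.

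**Step 1. Additions named per candidate (3.6.1.5).**

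| Dish | Sweetener | Fat | Flavouring |
|---|---|---|---|
| (a) | sugar | – | – |
| (b) | none named | – | cinnamon |
| (c) | honey | – | vanilla |
| (d) | sugar, by following (a) | butter | – |
| Control | none named | none named | none named |

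Candidates with at least one addition: 4 of 4.

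**Step 2. What any selected pair contains.** Choosing 2 of 4 gives 4 × 3 / 2 = 6 pairs.

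- Pairs with at least one addition: 6 of 6.
- Pairs with at least one dish for which sugar or honey is named: 6 of 6, because only (b) lacks a named sweetener and a pair needs a second dish.
- Pairs with butter: (d) with each of the other three, 3 of 6.

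So a named sweetener is certain in the experimental arm and butter depends on the children's choice.

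**Step 3. Differences that do not depend on the control recipe.** There are two dishes against one. The experimental dishes are selected for liking; the control is not. The paste has a provisional portion of 64 g; the control has none. These hold even if the control flesh turns out to be cooked with the same additions.

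**Step 4. What cannot be computed.** The 30 g of sugar belongs to a batch of unstated size, so the amount per child is unknown. The ratio of seed powder to flesh is not given, so the flesh eaten in each arm cannot be compared. No figure is given for an effect of any added ingredient on zinc, iron or growth. The direction and size of any bias therefore remain unknown.

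**The case against.** **The control may not be plain.** Section 3.6.3 describes the paste just as briefly, as ground seeds with cooked flesh, and mentions no sugar or butter there either. In recipe (a) the sugar goes in while the flesh is cooked, before the powder, and the powder is mixed with cooked flesh at the preschool. The same cooked flesh with and without powder is a possible reading. This stands: a reader might infer that the control certainly lacks every addition, but the documents are silent. The differences in step 3 remain on either reading.

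**No formal contradiction.** A reader might set the control against the phrase "while other variables are kept constant" in section 3.6.3.3. That phrase sits in a textbook account of randomised designs and is not a commitment about recipes.

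**Iron absorption.** A reader might infer that the butter or the flesh alters iron uptake. The documents do not support this: the remark on fat under dish (d) concerns vitamins, and section 1.6.1 names tomatoes and orange as the vitamin C sources, not butternut.

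**Better liking delivers the treatment.** A child who eats more of a well-liked paste receives more seed, and the adherence objective concerns the seed paste only. This stands for the delivery of seeds. It does not help when plate waste is compared between arms.

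**Laboratory outcomes.** Zinc and iron status are assayed, so a visible difference in food is not shown to bias their measurement. This stands.

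**The song is a further non-seed difference.** True, and matching the food would not remove it. It limits what the fix achieves but does not justify avoidable differences in the food.

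**Conclusion.** The point holds as a weakness in the choice and specification of the control. Two dishes selected for liking, all candidates for which contain a sweetener, fat or flavouring, are compared with one mashed-flesh food that has no stated recipe or portion. Read literally, the arms differ in recipe, variety and palatability besides the seeds. The difference in added ingredients rests on taking the control description at its word; the differences in number of dishes and in selection for liking do not.

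The consequence is weaker attribution to the seeds, most plausibly for anthropometry and intake. Nutritional status is a secondary, descriptive aim in section 2.3, so the effect on the main conclusion is limited. A bias in zinc or iron status is neither shown nor excluded. Because the hypothesis speaks of the paste and the aims speak of the seeds, the mismatch bears on how the result may be worded more than on whether the arms can be compared. This is worth correcting before phase three, but it does not invalidate the trial.

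**What to change.** Phase one has still to choose the recipes and settle the portion, so the control can be fixed at the same step. In section 3.6.3 and the schematic table:

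- Define the control as the same two selected recipes, prepared identically but without the seed powder.
- Use the same rotation of dishes and the same serving procedure in both arms.
- State the basis of the control portion (for example, equal total weight or equal amount of cooked flesh). The choice and the size are for the sponsor.
- Replace or explain the placebo label so that it agrees with this definition.
- State that conclusions refer to seed paste plus song, unless the song is matched as well.

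The cost is a few sentences and some ingredients. The downside is that control children receive the same sugar, honey, butter or spice. No extra children, visits or staff are needed.

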**3.3. Location of study:**

The study will be conducted at registered government preschools in the Vhembe district of Limpopo province in South Africa. Vhembe district is one of five districts of Limpopo province, and is divided into four municipalities namely Musina**,** Thulamela**,** Makhado and Collins Chabane (Lim 345). The Vhembe district has a total population of 1,294,722, with 703,226 (53.3%) females and 591,496 (46.7%) males, 1*14* 984 (12.7%) children under five years. Furthermore, 67.2% of this population speaks *Tshivenda,* 24.8% *Xitsonga*, 1.3% Afrikaans, and 1.6% *Sesotho sa Leboa*. The District has very high unemployment rate of almost 24% (Stats SA, 2011). The total number of pre-schools (ECDs) registered under Department of Social Development in the government are 730 in 2018. The total number of children in preschools around the Vhembe district is 40291 (Department of Social Development, 2018). The researcher, [name] *et al*. (2015) previously reported 42.6% zinc prevalence and 28% iron prevalence in preschools in Vhembe district.

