**3.4. Sampling**

Musina municipality will be purposefully selected from Vhembe District. These are in geographic proximity of the University of Venda where researcher is located and where the previous study was conducted ([name] *et al*., 2015). Simple random sampling will be used to select six preschools, three each from the two local municipalities. Simple random sampling is a sampling procedure, which provides equal opportunity of selection for each element in a population (Lee and Nieman, 2010). A list of pre-schools will be obtained from the Department of Social Development in Vhembe district and each pre-school will be assigned a number. The researcher will randomly select one number at a time. The following Slovin formula is used to calculate the total sample size used in the study: n = N/ (1 + (N X e^2^)) where

n= sample size

N= total number of children in the pre-schools; and

e = the accepted level of error

n = N/ (1 + (N X e^2^))

=40291/ (1+(40291 x 0.05)

=40291/ 101.7275.

= 396

= plus 10%

= 435.6

= 436

The formula yielded 396 participants, and an additional 10% will be added to account for attrition, making 436. Total sample size was calculated from the total number of children registered in the Early Childhood Development under Social Development in South Africa in 2017 in Vhembe district (Government Gazette, 2017). The sample frame will be six preschools, which are yet to be randomly selected. If the total number of participants in these six selected preschools does not reach the total number of 436, two more preschools will be added to the sample frame. The six preschools will be randomly assigned to the treatment or control.

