**3.7. Fieldworkers**

Five nutritionists will be recruited for monitoring, implementation of the feeding trial. The researcher will train field workers and methods of data collection will be standardized during piloting. The total team will be six including the researcher. Phlebotomist will be responsible for drawing blood as it is a requirement by the Health Professional Council of South Africa and these will be provided as part of the package from Ampath laboratories. The appointment of fieldworkers will be based on their expertise, which will be required for the study and for good general practice. There will be three teams with each visiting one primary school on the day of the feeding trial for monitoring. The table below illustrates the data collection responsibilities.

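### The feeding-trial table (eight preschools of 73, or 584 children) contradicts the stated 436 children in six randomised preschools, and the protocol's own counts make 436 hard to reach even with eight

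*Protocol*

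**What the plan says.** **Size and clusters.** Section 3.4 derives 396 children from the Slovin formula, adds 10% for attrition and arrives at 436. On preschools it says: "Simple random sampling will be used to select six preschools, three each from the two local municipalities". If enrolment in these six "does not reach the total number of 436, two more preschools will be added". It then says that the six will be randomly assigned to treatment or control.

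**Feeding-trial table.** The schematic in section 3.6.3 (captioned Table 3.3) has eight rows, four experimental and four control, each with an estimated 73 children. The last begins "Preschool 8 | 73 | Normal diet plus mashed butternut (placebo". No total is given.

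**Other places that depend on the size.** The visit days in section 3.6.2.4 are 6 for visit 2 and 12 for visits 3 and 4. Table 3.7 in section 3.10 budgets laboratory work for 436 children at two time points, at R759,076.

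**District counts.** Section 3.3 says "The total number of pre-schools (ECDs) registered under Department of Social Development in the government are 730 in 2018" and "The total number of children in preschools around the Vhembe district is 40291". Section 3.5 admits consented children aged 3–5 who are present on the day.

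**Staffing.** Below the table: "On intervention days, Monday to Thursday, the field workers and the researcher will be on site for quality control", in teams of two, one team per preschool. Section 3.7 adds: "There will be three teams with each visiting one primary school on the day of the feeding trial for monitoring". The intervention text in 3.6.3 has the meals served with the researcher and a trained field worker supervising.

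**The concern.** The number of clusters, the total size, the allocation and the supervised delivery depend on which part of the protocol is followed. A team working from section 3.4 would run six clusters and 436 children; a team working from the table would run eight clusters and 584. In a trial with so few clusters, that is a different design.

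The stated size also looks optimistic against the protocol's own district counts. If the drawn preschools are of ordinary size, six fall well short and the fallback becomes the likely course. Yet the allocation sentence in 3.4 still speaks only of the six, and the roster does not fit the sessions that eight preschools would need.

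**Working it through.** **1. The plan's own size reproduces.** N = 40291, e = 0.05 (section 3.4). n = N/(1 + N·e²) = 40291/(1 + 40291 × 0.0025) = 40291/101.7275 = 396.07. The printed line omits the square, but the divisor uses it. Then 396 × 1.10 = 435.6, rounded to 436.

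**2. Table against text.**
- 436/6 = 72.7 and 6 × 73 = 438, so 73 belongs to six preschools.
- 8 × 73 = 584, which is 148 above 436; 148/436 = 34%.
- Eight preschools sharing 436 would have 436/8 = 54.5 each.
- The fallback applies only if six fall short of 436. Six of exactly 73 give 438 and would not trigger it.

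**3. Budget.** The unit prices in Table 3.7 sum to 152.8 + 80.9 + 148.9 + 140.3 + 130 + 217.6 = R870.5. R870.5 × 872 = R759,076, exactly as printed, so the budget follows 436. For comparison only, 584 children twice would be R870.5 × 1168 = R1,016,744.

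**4. Reach at the district mean.** 40291/730 = 55.2 children per preschool; 73 is 32% above that.

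| Share of all children enrolled | Six preschools | Eight preschools | Average-sized preschools needed for 436 |
|---|---|---|---|
| 100% | 331 | 442 | 8 |
| 90% | 298 | 397 | 9 |
| 80% | 265 | 353 | 10 |
| 70% | 232 | 309 | 12 |

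Eight reach 436 only at 436/441.5 = 98.7% enrolment. The 70–90% range is an assumption; the protocol gives no consent rate, age split or attendance rate.

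**5. Sessions against teams.** Counting the tabled days:

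| | Mon | Tue | Wed | Thu | Fri | Total |
|---|---|---|---|---|---|---|
| Sessions, eight preschools | 4 | 2 | 4 | 4 | 2 | 16 |
| Covered by three teams, Mon–Thu | 3 | 2 | 3 | 3 | 0 | 11 |
| Sessions without preschools 4 and 8 | 4 | 2 | 2 | 4 | 0 | 12 |
| Covered | 3 | 2 | 2 | 3 | 0 | 10 |

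With eight preschools, 5 of 16 sessions (31%) have no team. Dropping to six by deleting preschools 4 and 8 still leaves 2 of 12 uncovered.

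**6. Allocation and municipality.** Preschools are drawn three per municipality, but allocation within municipality is not specified. If arms are equal at 3:3 (an assumption for six; the table shows 4:4 for eight), an unrestricted draw puts each municipality wholly in one arm with probability 2/C(6,3) = 2/20 = 10%.

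**The case against.** **The target is not out of reach.** A reader might infer that the stated design cannot deliver 436 children. The documents do not support that. Section 3.4 provides the fallback, and eight average-sized preschools hold about 442. The mean is district-wide, the trial draws from two of four municipalities, and no size distribution is given; larger preschools would change the picture. What stands is that near-complete enrolment is needed at the mean.

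**Eight preschools of about 73 are not impossible.** The column is an estimate. Six preschools averaging 72 give 432, which triggers the fallback, and eight would then hold about 576. But that total is still far from 436, and nothing caps enrolment in the table. Sections 3.4, 3.6.2.4 and 3.10 all fit six preschools and 436; the table alone is out of line. The R1,016,744 is therefore a comparison, not a planned cost.

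**Added preschools need not escape randomisation.** A reader might infer that preschools added under the fallback would undermine it. Section 3.6.3.3 says that participating preschools are randomly allocated, and section 3.4 adds them to the sampling frame before it speaks of allocation. The weakness is only that the allocation sentence names six and that no single step covering added preschools is described.

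**Unrestricted allocation is valid.** Allocating within municipality is an improvement, not the repair of an error. One might also infer that municipality carries language with it, but the protocol names both local languages for the two municipalities together and does not assign one to each.

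**Sessions without a team may still be watched.** Table 3.6 gives the preschool teacher or principal a monitoring role in phase 3. That does not meet the stated supervision by researcher and field worker.

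**Conclusion.** The contradiction is established from the protocol alone: six randomised preschools and 436 children in one place, eight preschools and an implied 584 (34% more) in another, with the blood budget and visit days following the smaller plan. The 73 per preschool is the six-preschool figure.

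The shortfall is an expectation, not a certainty. It rests on the district mean applying to the drawn preschools: about 331 in six and 442 in eight at full enrolment, and about 309–397 in eight at an assumed 70–90%.

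The staffing conflict is also established: 11 of 16 tabled sessions are covered by three teams on four days, or 10 of 12 with preschools 4 and 8 removed.

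A reader might want to turn six against eight clusters into a difference in detectable effect. The protocol gives no intracluster correlation, so no such figure is offered here.

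This should be corrected before preschools are allocated, because the size and cluster count that the trial relies on disagree and can be restated cheaply.

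**What to change.** 1. Obtain the registers of the drawn preschools and settle the number of preschools from them before allocation.
2. Select all preschools, including any added under the fallback, before a single randomisation step, and replace the reference to six in the allocation sentence of section 3.4 with the full set.
3. Allocate within municipality, since the draw is already made that way: 2:2 in each if eight, or 2:1 and 1:2 if six.
4. Replace 73 with the figure that matches the chosen number. Restate the expected total, below 436 if registers and likely uptake do not support it. Simply writing 54 or 55 in eight rows would assume almost complete enrolment at the district mean.
5. Carry the same numbers through section 3.4, the visit days in 3.6.2.4, the feeding-trial table and the budget in 3.10.
6. Reconcile the statements on feeding days, supervision, team numbers and team days in sections 3.6.3, 3.7 and 3.10, where field workers are funded for four days a week. Which days are right is for the investigators to decide.

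The cost is mainly wording, one randomisation step and a re-planned roster. The downside is that the honest total may be less favourable than 436, and more preschools would need more team sessions than the present roster provides.
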